### Statistical Considerations

Data analysis will be performed using the IBM SPSS Statistics 24 statistical software package (SPSS, Inc., Chicago, IL). First, all data will be checked for normality of distribution using the Shapiro-Wilk test. Results will be expressed as means (with standard deviations) for continuous and normally distributed variables and as medians (with interquartile ranges) when normality of data cannot be assumed. Categorical variables will be described in frequency counts and percentages. Tests for baseline comparisons will be selected based on the nature and distribution of the data: Student's-t test for continuous and normally distributed variables, Mann-Whitney test for non-normally distributed continuous variables, and Chi-squared test for categorical variables. To test the effects of training interventions, mixed-designed ANCOVA-s or the Friedman test, including baseline measurements as covariates, will be performed for all studied variables. In cases where a significant F-value is found, LSD *post hoc* procedures will be performed for pair-wise comparisons. The level of statistical significance will be set at *p* < 0.05 for all computations.

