### Inclusion and Exclusion Criteria, Recruitment, and Randomization

Subjects will be considered eligible for the study if they fulfill all of the following criteria: (a) aged ≥ 18 years, (b) diagnosis of MS according to McDonald criteria (45), (c) moderate to severe gait impairments defined by an Expanded Disability Status Scale (EDSS) score ranging from 4.5 to 7 (46), and (d) the need for one or two canes or crutches for walking outdoors.

Participants will be excluded if they (a) have a neurological pathology in addition to MS, (b) have some musculoskeletal disorder that could limit the extension of the hip and knee or the plantar flexion of the ankle, (c) have suffered an outbreak of MS during the 3 months prior to the start of the study, (d) are under non-stable pharmacological treatment or with treatments expected to be modified during the study, or (e) have received treatment with botulinum toxin in the 12 weeks prior to the beginning of the study.

Recruitment will be done at ADEMBI. Informative meetings will be organized to provide detailed oral and written information about the study, including objectives, studied variables, and methodology, to both potential participants and their families. Participants will sign, indicating informed consent, after fully understanding the study. Using a coin-tossing sequence generation, participants will be randomly allocated at a 1:1 ratio to either the control group (CG) or the intervention group (OR). The assignment will be conveyed via sealed opaque envelopes.

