### Sample Size Calculation

Sample size has been calculated to detect a clinically meaningful change in gait speed: accepting an alpha risk of 0.05 and a beta risk of 0.20 in a bilateral contrast, 32 subjects are required to detect a difference equal to or greater than 0.1 m/sec speed in the 10 meters timed walking test (SD = 0.16). Sample size has been increased an additional 12% to account for losses during follow-up. The resulting sample size is 36 subjects, therefore 18 individuals per group (intervention and control group).

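### The gait-speed ANCOVA adjusts only for baseline measurements and leaves out EDSS, which is known for every participant; pre-specifying EDSS costs little and brings a modest gain

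*Protocol article*

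**What the plan says.** All references are to the protocol article.

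- **Model (Statistical Considerations).** To test the training effect, "mixed-designed ANCOVA-s or the Friedman test, including baseline measurements as covariates, will be performed for all studied variables". No other covariate is named.
- **Baseline table (same section).** "Tests for baseline comparisons will be selected based on the nature and distribution of the data": Student's t, Mann-Whitney or chi-squared. The threshold is general: "The level of statistical significance will be set at *p* < 0.05 for all computations". The section does not say what follows from a significant or a non-significant baseline result.
- **EDSS (Inclusion and Exclusion Criteria, Recruitment, and Randomization).** Eligibility requires "moderate to severe gait impairments defined by an Expanded Disability Status Scale (EDSS) score ranging from 4.5 to 7", so a score exists for every participant. EDSS is absent from the assessments listed under Secondary Outcomes.
- **Allocation (same section).** 1:1 by coin toss; no stratification is described.
- **Size (Sample Size Calculation).** 32 participants for a gait-speed difference of 0.1 m/s with SD 0.16, raised to 36, which is 18 per arm.

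**The concern.** Coin-toss allocation of 36 people can leave the arms different in disability, and EDSS 4.5 to 7 is a broad range for a walking outcome. Adjusting for baseline gait speed removes the part of such a difference that baseline speed carries. It does not remove what EDSS predicts beyond baseline speed. A covariate fixed in advance would protect against that part and lower the residual variance, using data already collected. If EDSS is added only after an imbalance is seen, the adjustment is post hoc and open to challenge.

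The planned baseline tests do not fill this gap. After randomisation any baseline difference is due to chance. Its effect on an outcome depends on its size and on how prognostic the variable is, and a p-value measures neither.

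**Working it through.** **Inputs from the article.** Target difference 0.1 m/s; SD 0.16; two-sided alpha 0.05; power 0.80; 32 evaluable (16 per arm) and 36 randomised (18 per arm).

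**Assumptions, not in the article.** Correlation r of baseline with follow-up speed; partial R² (or partial r) of EDSS given baseline speed; an illustrative EDSS imbalance of 0.6 SD.

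**1. The plan's own sample size.** Per arm: 2 × (1.960 + 0.842)² × 0.16² / 0.1² = 40.2, so 41 per arm or 82 in total. The stated 32 does not follow from a plain two-group comparison with these inputs. It would follow from an ANCOVA with r of about 0.78, since 40.2 × (1 − r²) = 16, but no correlation is stated. This is a separate matter. It is relevant here only because 16 per arm leaves little precision to spare.

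**2. Power with and without EDSS, 16 per arm.** Residual SD = 0.16 × √(1 − r²) × √(1 − partial R²). Noncentrality = 0.1 / (residual SD × √(2/16)). Residual df are 32 − 3 = 29 without EDSS and 28 with it, so the lost degree of freedom is already charged. For r = 0.7:

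| EDSS partial R² | Residual SD | Noncentrality | Power |
|---|---|---|---|
| not in model | 0.1143 | 2.475 | 67% |
| 5% | 0.1114 | 2.540 | 69% |
| 10% | 0.1084 | 2.609 | 71% |
| 15% | 0.1053 | 2.685 | 74% |

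For r = 0.5 the same steps give about 51% without EDSS and 52%, 55% and 57% with it. At r = 0.7 and partial R² of only 2%, power goes from 66.7% to 67.5%.

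**3. Shift from a chance EDSS imbalance.** Shift = partial r × 0.16 × √(1 − r²) × 0.6. The 0.6 SD must be what remains after adjustment for baseline speed.

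| Partial r | r = 0.6 | r = 0.8 |
|---|---|---|
| 0.2 | 0.015 m/s | 0.012 m/s |
| 0.4 | 0.031 m/s | 0.023 m/s |

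This is about 0.01-0.03 m/s. With partial r from 0.1 to 0.5 the range widens to 0.006-0.038 m/s.

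If the 0.6 SD is instead the raw imbalance and EDSS correlates ρ with baseline speed, the expected remainder is 0.6 × √(1 − ρ²). For ρ = 0.4 to 0.7 that is 0.55 to 0.43 SD. At r = 0.7 the shift is then 0.013 to 0.010 m/s for partial r 0.2, and 0.025 to 0.020 m/s for partial r 0.4.

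**4. How often.** At 18 per arm the standard error of a standardised difference is √(2/18) = 0.333. P(|Z| > 0.6/0.333 = 1.8) = 0.072, so a raw imbalance of 0.6 SD or more arises in about 7% of randomisations.

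**5. What a baseline t-test can flag.** t(0.975, 34) × 0.333 = 2.032 × 0.333 = 0.68 SD. An observed 0.6 SD gives t = 1.80 and p = 0.081. Imbalances from 0.6 SD up to the threshold arise in about 0.072 − 0.042 = 3% of randomisations.

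**The case against.** **The covariate list belongs in the analysis plan, which is not shown.** This is the strongest objection. It would succeed if the article were silent, but the article states the covariate set, and the point concerns that stated model. If the full plan already names EDSS, nothing needs to change except the article's summary.

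**The stated model is valid.** This stands. Under randomisation an ANCOVA on the outcome's own baseline gives a valid test. The shift in step 3 is conditional on an unlucky allocation; it is not a bias over repeated randomisations.

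**The benefit is small and assumed.** This largely stands. No correlation is in the article, and EDSS probably overlaps with baseline speed, since the article uses EDSS to define the gait impairment. More overlap means less gain.

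**Stronger readings that a reader might infer, and that the article does not support:**

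- *The tests will decide whether the arms are comparable, or which covariates are used.* The section attaches no consequence to them, and the baseline covariate enters whatever they show. Dropping them changes no planned estimate.
- *A baseline gait-speed gap as large as the target could pass unflagged and distort the result.* The threshold of 0.677 SD is 0.677 × 0.16 = 0.108 m/s, but the ANCOVA already adjusts for baseline gait speed.
- *The tests cannot flag a 0.6 SD imbalance in EDSS.* This is exact only for a t-test on an observed difference. In simulations with two assumed distributions of a six-level EDSS, a Mann-Whitney test flagged about 2-9% of imbalances near 0.6 SD. The article does not even say that EDSS will be among the variables tested.

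**Conclusion.** The point holds as an improvement to a stated model. EDSS is available for everyone, is plausibly prognostic for walking, and is left out of an ANCOVA with 16 to 18 people per arm and no described stratification. The expected gain is about 2 to 7 percentage points of power if EDSS has a partial R² of 5-15%, and close to nothing if it adds little beyond baseline speed. The protection is against a conditional shift of about 0.01-0.03 m/s, which is 10-30% of the target, in the minority of allocations with a large remaining imbalance. These sizes depend on correlations that the article does not give, and on reading baseline measurements as the outcome's own baseline value.

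The baseline significance tests are a secondary reporting matter. They answer no useful question in a randomised trial, but they affect no planned estimate.

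**What to change.** In Statistical Considerations, state: 'The ANCOVA for gait speed, and for the other outcomes analysed by ANCOVA, will include the outcome's baseline value and EDSS at entry as pre-specified covariates, regardless of any observed baseline difference.' The article describes the trial as ongoing, so this should be recorded before outcome data are analysed by arm.

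As a reporting change, replace the baseline-test sentence with: 'Baseline characteristics will be described by arm without significance tests.'

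The cost is two sentences, no new data and one residual degree of freedom per model, 1/29 or about 3% of those available. If EDSS proves uninformative, that degree of freedom is the only loss.

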## Materials and Methods

### Study Design and Participants

This is a prospective parallel-assignment, single-blinded, randomized controlled study. Participants will be randomly assigned to one of the following groups: the control group (CG) or the OR group. The study will take place at the Asociación de Esclerosis Múltiple de Bizkaia (ADEMBI) between January 2019 and December 2019. The assessments will be conducted by blinded research staff at baseline (T1) and after 3 months of training (T2). After a 3-month follow-up period, a final assessment will be performed at 6 months (T3). The study has been designed and results will be reported according to the CONSORT Statement extension for trials of non-pharmacological interventions and pragmatic intervention trials (Figure 1

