### Primary Outcome: Gait Speed

The assessments will be performed at ADEMBI by blinded research staff at baseline (T1), 3 months (T2), and 6 months (T3). Participants will walk through a 10-meters corridor at their own habitual speed. The time spent in performing the test will be measured through photoelectric cells (Polifemo, Microgate, Italy), and afterwards, gait speed calculated Participants will be allowed to wear their own footwear, orthoses, and prescribed usual assistive device (crutches, canes). This test will be performed as the first assessment to avoid possible muscle fatigue.

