### Secondary Outcomes

Secondary outcomes will include physical and cognitive performance tests (Table 2), and clinical, fatigue and quality of life assessments (Table 3), and the measurement of circulating inflammatory cytokines.

**Table 2 T2:** Physical and cognitive assessment tests and questionnaires.

**Test (references)**	**Functions/Parameters**	**Description**
Handgrip strength test (Jamar dynamometer) (46)	Dominant hand grip strength	Squeeze the dynamometer with maximum isometric effort for about 5 s
Timed Up and Go test (47)	Dynamic balance	Get up from a chair without upper-limb assistance, walk 3 m at a normal pace, turn and sit back in the chair
Short Physical Performance Battery (SPPB) (48)	Lower extremity function: static balance, gait speed, and getting in and out of a chair	Side-by-side, semi-tandem, and tandem stands (10 s); 4 m walk test at comfortable speed; and 5 quick sit to stands from a chair without upper-limb assistance
Berg balance test (49)	Postural stability	Performance of 14 functional tasks
Yale Physical Activity Scale (50)	Physical activity	Type, amount, pattern, and perceived difficulties of performed physical activities throughout daily living
Montreal Cognitive Assessment (MoCA) (51)	Cognitive dysfunction	Covered domains: attention and concentration, executive functions, memory, language, visuoconstructional skills, conceptual thinking, calculations, orientation

**Table 3 T3:** Muscle spasticity, fatigue, and health related quality of life assessment tests and questionnaires.

**Test (References)**	**Functions/Parameters**	**Description**
Modified Ashworth Scale (MAS) (52)	Spasticity	Graduation of the resistance encountered during passively stretching flexor and extensor muscle groups of bilateral hip, knee, and ankle
Modified Fatigue Impact Scale (MFIS) (53)	Physical and mental fatigue	21-item scale measuring perceived fatigue over the last four weeks
EuroQol-5 (54)	Health related quality of life	Covered domains: mobility, self-care, usual activities, pain/discomfort, and anxiety/depression

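### The mixed-design ANCOVA (or Friedman test), in its usual form, makes the end-of-training (T2) comparison depend on attendance at T3

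*Protocol article*

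**What the plan says.** The Statistical Considerations section fixes one approach for every outcome: "To test the effects of training interventions, mixed-designed ANCOVA-s" or, as the alternative, the Friedman test, with the baseline value as covariate. The software is given ("Data analysis will be performed using the IBM SPSS Statistics 24 statistical software package"), but not the procedure within it.

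Study Design and Participants sets three assessments: baseline (T1), the end of the 3-month training period (T2), and 6 months (T3), after 3 months of follow-up. Gait speed is measured at all three, and no visit is designated primary.

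The Sample Size Calculation section expects attrition: "Sample size has been increased an additional 12% to account for losses during follow-up". This takes 32 participants to 36, or 18 per arm.

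The article names no analysis set, no rule for incomplete cases, and no value for a participant who cannot complete the walk.

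**The concern.** A mixed-design (between-within) ANCOVA is the classical repeated-measures model. As usually run in SPSS, through the repeated-measures general linear model, it needs a complete row for each participant, so one missing visit removes the person from every visit. The Friedman test ranks within complete blocks and has the same requirement.

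In this trial T2 answers whether the training works and T3 answers whether the effect lasts. A participant who completes training, is measured at T2 and then does not return contributes a valid randomised observation to the first question. Under the named methods in their usual form, that observation is discarded.

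Two things are at stake. The first is precision, in a trial of 36 people with little to spare. The second is that the T2 estimate is restricted to people who also attend at 6 months. If later attendance is related to walking ability or to arm, that restriction can distort the comparison.

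**Working it through.** **Inputs from the article.** Target difference 0.1 m/s; SD 0.16 m/s; two-sided alpha 0.05; power 0.80; 32 participants required; 12% loss allowance; 36 randomised, 18 per arm; visits T1, T2 and T3.

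**Inputs assumed.** The split of the 12% loss between the two intervals, and the correlation r of baseline with follow-up gait speed. The article gives neither, so ranges are shown.

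**The plan's own figures.** The inflation step reproduces: 32 × 1.12 = 35.84, rounded up to 36. (Dividing instead, 32/0.88 = 36.4, gives 37.) The 32 does not follow from the stated inputs for a two-arm comparison: 2 × (1.960 + 0.842)² × 0.16² / 0.1² = 40.2, so 41 per arm or 82 in total. A total of 32 with a two-sided test needs an unstated r of about 0.776, that is a residual SD of about 0.101. That is a separate matter and this point does not rest on it. It is used below only as one value of r.

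**Step 1: numbers contributing to T2.** Complete cases number 36 × 0.88 = 31.7, about 32, wherever the loss falls. The people with a T2 value depend on timing. The standard-error ratio is √(T2 available / complete cases).

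| Loss by T2 / between T2 and T3 | T2 values available | Complete cases | SE ratio |
|---|---|---|---|
| 0% / 12% | 36 | 31.7 | 1.066 |
| 3% / 9% | 34.9 | 31.7 | 1.050 |
| 6% / 6% | 33.8 | 31.7 | 1.034 |
| 12% / 0% | 31.7 | 31.7 | 1.000 |

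With whole people in the first row, √(36/32) = 1.061.

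**Step 2: power at T2 when all loss falls between T2 and T3.** Residual SD = 0.16 × √(1 − r²); SE = residual SD × √(2/n per arm); power = Φ(0.1/SE − 1.96).

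- r = 0 (SD 0.16): 18 per arm, SE 0.0533, power 0.466; 15.84 per arm, SE 0.0569, power 0.420.
- r = 0.776: 18 per arm, SE 0.0336, power 0.844; 15.84 per arm, SE 0.0359, power 0.796.

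Using the t distribution and 16 against 18 per arm, r = 0.6 gives 0.570 against 0.624, and r = 0.8 gives 0.813 against 0.858. In every case the drop is 4 to 5 percentage points.

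**Step 3: does deletion bias the T2 estimate?** This was simulated with 18 per arm, mean 0.5 m/s, SD 0.16, correlations 0.70 to 0.78 and a true T2 effect of 0.10 (mean and correlations assumed). T2 was complete and four people were missing at T3.

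| Who is missing at T3 | Estimate, all T2 data | Estimate, complete cases |
|---|---|---|
| Four at random | 0.099 | 0.099 |
| The four slowest, either arm | 0.100 | 0.092 |
| The four slowest controls | 0.100 | 0.085 |

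Random loss costs precision only: the SE goes from 0.0336 to 0.0359. Loss related to outcome pulls the complete-case estimate away from 0.10, while the estimate from all T2 values stays at 0.10.

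**The case against.** The strongest reply is that complete-case deletion is inferred. The article names neither a procedure nor a deletion rule, and SPSS 24 can also fit a model that keeps partial data. That is correct. The point therefore concerns the named methods in their usual form and is not a claim that the authors announce deletion. It still has force, because both named methods ordinarily require complete data.

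Second, the loss of numbers is budgeted: about 32 complete cases is what the sample size section says it needs. That stands as far as the headcount goes. It does not justify discarding T2 values that have been collected. The 6% and 4-to-5-point figures are also a worst case over the timing of loss, as the tables show.

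Third, handling of missing data may sit in a fuller document that is not shown. Its absence from an article is not held against the plan here; the point is about a method the article does fix.

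A reader might infer more: that the method removes the trial's worst outcomes from its primary T2 comparison. Speed is derived from a recorded time ("The time spent in performing the test will be measured through photoelectric cells"), so an uncompleted walk yields no speed, and Timed Up and Go is described as "Get up from a chair without upper-limb assistance, walk 3 m at a normal pace" in people who need canes or crutches. The documents do not support that reading. T2 is not designated primary, nothing says people unable to perform a test are deleted, and no number or arm pattern of such people is given. A scoring rule may exist elsewhere. Scoring inability as 0 m/s, or as the worst rank for Timed Up and Go, also changes the quantity being estimated, which is a debatable choice and not the correction of an error.

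**Conclusion.** The point holds in a limited form. A mixed-design ANCOVA or Friedman test over these visits, run in the usual way, would remove from the end-of-training comparison anyone who is measured at T2 but missing at T3. The cost in standard error at T2 ranges from nil (all loss by T2), through about 3% (even split), to about 6% with 4 to 5 points of power (all loss between T2 and T3). These figures rest on the planned 12% loss being realised and on assumed timing and correlation. Bias is possible but conditional on loss being related to outcome or arm, and nothing in the article shows that it will be. The change is worth making because a better method is available in the same software at little cost.

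**What to change.** In Statistical Considerations, replace the mixed-design ANCOVA for gait speed with a linear mixed model for repeated measures (SPSS MIXED, REML). The outcomes are the T2 and T3 values. The fixed effects are baseline gait speed, group, visit, group-by-visit and baseline-by-visit, with an unstructured covariance. Include all randomised participants, by assigned arm, who have any post-baseline value. Report the group difference at T2 and at T3 from this one model; a missing T3 then no longer removes a T2 value.

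Cost: a change of wording, slightly more analysis work, and reliance on a missing-at-random assumption, which should be stated. No extra visits or tests are needed.

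Optional, as a suggestion and not a correction: have assessors record unable to complete separately from not done, and report a sensitivity analysis that scores inability on the 10 m walk as 0 m/s. The article's Trial Status section says the trial is already under way, so this distinction may not be recoverable for visits already completed.

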Therefore, this study aims to determine the effects of the addition of an OR intervention to the conventional rehabilitation program on gait speed in people with MS and moderate to severe walking disabilities. As a secondary aim, the study will determine the effects of the intervention from a multidimensional perspective, taking into account physical, cognitive and clinical parameters, fatigue and health-related quality of life of the participants. Additionally, as MS is accompanied or mediated by neuro-inflammation, training interventions may stimulate an anti-inflammatory response contributing to the positive effects of exercise in patients with MS (43, 44). Thus, the influence of the intervention on peripheral inflammatory cytokines will also be analyzed. Finally, this study aims to ascertain if the effects of the intervention are maintained over a follow-up period of 3 months.

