Participants will self-report their age, gender, marital status, employment situation, and Barthel index (49). Physical and cognitive examination will include the following (Table 2): the handgrip strength test (50) (Jamar dynamometer), Timed Up and Go test (51), Short Physical Performance Battery test (52) (SPPB), Berg balance test (53), Yale Physical Activity Survey (54) (YPAS), and Montreal Cognitive Assessment (55) (MoCA). Clinical information will be determined by the Modified Ashworth Scale (56) (MAS) and the number of outbreaks and falls during the studied period. Fatigue will be assessed by the Modified Fatigue Impact Scale (MFIS) (57) and health related quality of life by the EuroQol-5 [(18); Table 3].

Plasma levels of pro-inflammatory (Interferon γ, Interleukin-12, Tumor necrosis factor-α, Interleukin-17, and Interleukin-6) and anti-inflammatory (Interleukin-6, Interleukin-4, Interleukin-13, Interleukin-10 and Tumor growth factor-β) cytokines will be assessed using Simoa HD-1 technology. Assays will be performed according to the manufacturers' instructions. Briefly, a two-step assay procedure will be utilized. Standards will be prepared with calibrator diluent according to lot-specific concentrations provided by the manufacturer. Samples will be prepared as directed using a sample diluent off-line.

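### The Friedman test, named as the alternative to mixed ANCOVA, has no group term and takes no covariate, so any outcome sent to it gets no test of OR versus CG

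*Protocol article*

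**What the plan says.** Study Design and Participants describes the trial thus: "This is a prospective parallel-assignment, single-blinded, randomized controlled study". Participants go to "the control group (CG) or the OR group" and are assessed at baseline (T1), 3 months (T2) and 6 months (T3). The Introduction gives the aim as to "determine the effects of the addition of an OR intervention to the conventional rehabilitation program on gait speed". That is a contrast between arms.

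Statistical Considerations opens by stating that "all data will be checked for normality of distribution using the Shapiro-Wilk test". It uses normality to choose summary statistics and the tests for baseline comparisons, where Mann-Whitney is the rank option. For the intervention effect it then says that "mixed-designed ANCOVA-s or the Friedman test, including baseline measurements as covariates, will be performed for all studied variables". Post hoc LSD comparisons follow a significant F-value. The section does not say when Friedman replaces ANCOVA.

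Among the clinical variables, Secondary Outcomes lists "the number of outbreaks and falls during the studied period".

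**The concern.** The sentence gives the Friedman test a purpose that it cannot serve and a covariate that it cannot hold. No other part of the section fills the gap. The only between-group rank test named, Mann-Whitney, is assigned to baseline. The post hoc rule needs an F-value, whereas Friedman yields a chi-square statistic.

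An analyst who followed the text for a non-normal outcome would therefore have no test of the randomised comparison. Two substitutes are likely, and both mislead. Pooling the arms tests whether values change over time. Running the test in each arm gives two within-arm p-values, and a difference in their significance is not a test of the difference between arms.

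A shared time trend is plausible here. Both arms receive physiotherapy, and the Introduction reports a trial of robot-assisted gait training in which both arms gained gait speed with no group-by-time interaction.

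**Working it through.** **1. Structure of the test.** Rank each subject's k values, and let R_j be the rank sum of visit j over N subjects. Then

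Q = 12 / (N k (k+1)) × ΣR_j² − 3N(k+1), referred to chi-square with k−1 degrees of freedom.

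For k = 3 this is Q = ΣR_j² / N − 12N. Neither arm nor a covariate appears. Relabelling subjects between arms leaves Q unchanged.

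**2. Two extreme cases, N = 32 (16 per arm).**
- All 32 subjects rise steadily (ranks 1, 2, 3), with no difference between arms in pattern: R = 32, 64, 96. Q = (1024 + 4096 + 9216)/32 − 384 = 448 − 384 = 64, which is overwhelmingly significant.
- All 16 OR subjects rise (1, 2, 3) and all 16 CG subjects fall (3, 2, 1), the largest possible difference in pattern: R = 64, 64, 64. Q = 12288/32 − 384 = 0.

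**3. The covariate clause.** If baseline is kept out as a covariate, only T2 and T3 are left to rank. With k = 2 the test reduces to a sign test of whether values change between the end of training and follow-up. If baseline is one of the ranked visits, it is not a covariate. Neither version compares the arms.

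**4. Illustration on the gait-speed scale.** Inputs from Sample Size Calculation: SD 0.16 m/s and 32 evaluable subjects, so 32/2 = 16 per arm. Assumptions not in the documents: normal data, a gain of 0.05 m/s from T1 that persists at T3, and a common correlation between visits. With the same gain in both arms, and so no treatment effect, the share of simulated trials with p<0.05 was:

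| Visit correlation | Pooled Friedman | Per-arm Friedman, significant in OR only |
|---|---|---|
| 0.5 | about 31% | about 15% |
| 0.8 | about 66% | about 23% |
| 0.9 | about 93% | about 22% |

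The 0.5 row varied slightly between runs (31% to 33% pooled). A valid between-arm test would reject in about 5%.

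**5. Illustration with skewed data, where Friedman would more plausibly be chosen.** Assumptions: log-normal outcome, 18 per arm, between-subject SD 0.7 and within-subject SD 0.5 on the log scale, 3,000 runs.
- Same log shift of 0.4 in both arms: pooled Friedman rejects in 85%, against 4.8% for Mann-Whitney on the T1-to-T2 log change. Per-arm Friedman is significant in exactly one arm in 50%.
- Shifts of +0.4 in OR and −0.4 in CG: pooled Friedman 3.4%, Mann-Whitney on change 88%.

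**6. Falls and outbreaks.** These are counts over the study period, and the plan gives them no baseline value. An outbreak in the 3 months before the start is an exclusion criterion, so a pre-study count over that window would be zero for everyone. Neither a baseline covariate nor ranking across T1, T2 and T3 applies as written.

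**The case against.** The strongest reply is that mixed ANCOVA is named first, includes a group factor, and will serve for gait speed unless it is judged non-normal. This stands. A reader might infer that the primary outcome has no valid between-group test, and the document does not support that. The exposure of gait speed is conditional. For truly normal data, in simulation, Shapiro-Wilk would reject in about 5% of trials if applied once, about 12% if applied at each of three visits, and about 25% if applied to all six arm-by-visit cells. The article does not say which of these is meant, nor how gait speed is distributed.

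A reader might also take the Shapiro-Wilk result to be the written switch to Friedman. It is not. The switch is implied by the order of the paragraph and by its pairing of parametric with rank tests.

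Third, the percentages depend on assumed correlations and shifts. A claim that pooled Friedman has no power would go too far, because near-zero rejection needs shifts that cancel. With +0.10 m/s in OR and none in CG, at correlation 0.8, it rejects in about 55% of trials, though what it detects is still change over time.

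Finally, a condensed article may leave details to an unseen analysis plan. That covers the choice of model for counts or ordinal scales. It does not cover naming a test that cannot answer the stated question.

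**Conclusion.** The point holds as an error of method in what the article states. Any outcome sent to the Friedman test gets no OR-versus-CG comparison, and the baseline-covariate clause cannot be carried out with it. This follows from the form of the test and needs no simulation.

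The reach is narrower than the words on all studied variables might suggest. It is a clear risk for ordinal and skewed secondary outcomes such as the Ashworth grades, EuroQol domains and cytokines. For gait speed it arises only if that outcome is judged non-normal.

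The size of the possible error is illustrative: about 31% to 93% false signals from pooled Friedman, and about 15% to 23% significant in OR only, for visit correlations of 0.5 to 0.9 and an identical 0.05 m/s gain in both arms. The correlation and the gain are assumptions.

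**What to change.** - Delete the Friedman test.
- Fix the primary analysis of gait speed as the baseline-adjusted between-group ANCOVA, whatever Shapiro-Wilk shows. Check the residuals, and add a permutation or bootstrap analysis as sensitivity.
- For non-normal secondary outcomes, name in advance one between-group method that uses baseline. ANCOVA on a transformed scale gives an estimate with a 95% CI. Rank ANCOVA (Quade) or Mann-Whitney on change from baseline are valid alternatives, but do not by themselves give an effect estimate on the outcome scale.
- Compare falls and outbreaks directly between arms as counts. The exact count model can be left to the analysis plan.

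The cost is a wording change and minor analysis work on data already planned. Trial Status describes the trial as ongoing, so the change can be made and dated before the analysis.
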